### Study outcomes

#### Primary outcome

The primary outcome is the incidence of hypoxemia and severe hypoxemia [20].

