After adequate preoxygenation, anesthesia is induced with intravenous injection of propofol 2 mg/kg (10 mg/1 mL; Diprivan, Astrazeneca, UK). The depth of anesthesia is assessed by an anesthesiologist blinded to the group assignment. During the gastroscopy, 20–30 mg of propofol are supplemented as necessary to maintain an Observer’s Assessment of Alertness/Sedation score of 2 or 3 [19]. For patients receiving the WNJT, an appropriate size (ID 5.0 or 7.0 mm) device is selected by examining the outer diameter of the device and the patient’s nostrils. The device that is large enough but can be easily inserted through the nostril is selected. The WNJT is lubricated with 2% lidocaine gel (Jumcan Pharmaceutical Group, China) before insertion. The distance between the tip of the nose and earlobe on one side is measured using the scale on the exterior wall of the WNJT. After adequate anesthesia is achieved, the WNJT is inserted to the measured depth in the group A and the nasal prongs are placed in the group B. The position of the WNJT is re-examined by gastroscopy and adjusted for appropriate if necessary. The ideal position is designed as the distal tip of the WNJT is within 1 cm of the epiglottis tip. If insertion of WNJT is difficult via the selected nasal passage, the other side can be tried. If it is still unsuccessful after three attempts, insertion of the WNJT is regarded as a failure. During the gastroscopy, 5 L/min of oxygen is delivered directly through the jet port of the WNJT without using a jet ventilator in the group A and via the nasal prongs in the group B, respectively. Both the WNJT and nasal prongs are removed before the patients recover consciousness. Consequently, the patients are also blinded to the grouping assignment.

Throughout the gastroscopy, if hypoxemia (SpO_2_ < 90%) occurs, the taken measures include [4–6]: (1) audio or painful stimulation; (2) no additional drugs; (3) increasing the volume of oxygen from 5 to 8 L/min; (4) airway opening with the jaw-thrust maneuver; (5) removing the gastroscope tube and performing facemask ventilation; and (6) tracheal intubation for mechanical ventilation if necessary.

During the study, if nasal bleeding occurs in the group A, compression hemostasis is first performed; if it does not work, other medical or surgical measures should be considered.

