#### Data about the procedure

The BP, HR, and SpO_2_ during the endoscopy are recorded every 2 min. Total propofol dose, recovery time, hypoxemia, severe hypoxemia, times required for use of assistant airway maneuvers (jaw-thrust, mask ventilation, and tracheal intubation), adverse events during the endoscopy procedure (body movement, vomiting, regurgitation and aspiration, bronchospasm, cough, bradycardia, tachycardia, hypertension, hypotension), nasal bleeding, and recovery delay are also recorded.

In this study, hypoxemia is defined as SpO_2_ of 75–89% for < 60 s, and severe hypoxemia is defined as SpO_2_ < 75% at any time or SpO_2_ of < 90% for > 60 s [20, 21]. Hypotension is defined as a decrease in mean arterial pressure (MAP) > 20% or non-invasive blood pressure of not more than 90/60 mmHg; hypertension is defined as an increase in MAP > 20% or non-invasive blood pressure of at least 140/90 mmHg; bradycardia is diagnosed if HR is < 50 beats/min; tachycardia is diagnosed when HR stays above 100 beats/min. If necessary, ephedrine or phenylephrine, urapidil, atropine, and esmolol were intravenously injected to treat hypotension, hypotension, bradycardia and tachycardia, respectively [21–23].

Nasal bleeding is assessed using a subjective scale: 0, no bleeding; 1, minimal bleeding not requiring suctioning; 2, moderate requiring suctioning but not hampering visualization, and 3, severe requiring suctioning and hampering visualization [24].

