### Sample size estimation and statistical analysis

The sample size is calculated with the Pass software (version 11.0, NCSS, LLC, Kaysville, UT, USA). The two independent proportions procedure is used. With an α = 0.05 and a power of 80%, we estimated that 140 patients per group would be required for our study. If the dropout rate is set at about 10%, a total of 308 patients (154 in each group) would be required. The incidence of hypoxemia during gastroscopy in obese patients with intravenous propofol anesthesia has been reported to be 22% [20]. Thus, a proportion of 22% of the patients in the group B is expected to develop hypoxemia. P1 and P2 are calculated from the assumption that the WNJT would achieve a reduction from 22% to 11% for the incidence of hypoxemia.

Statistical analysis of data will be performed using the SPSS (Version 23.0, SPSS Inc., Chicago, IL, USA) by a blinded statistician. Continuous variables will be presented as mean ± standard deviation (normally distributed data) or medians and ranges (non-normally distributed data). Numerical data will be compared using a Student’s t-test (normally distributed data) or Mann–Whitney rank sum test (non-normally distributed data). Qualitative data will be expressed as n (%) and compared using a Chi-squared test. A *P* value < 0.05 is considered statistically significant.

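### The primary endpoint is not fixed: hypoxemia is defined without the severe episodes, the primary outcome names both without saying how they combine, and the sample size rests on hypoxemia alone.

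*Protocol article*

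**What the plan says.** Four places in the protocol article bear on the primary comparison.

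- **Primary outcome:** "The primary outcome is the incidence of hypoxemia and severe hypoxemia". Nothing says whether the two are combined, both required, or each sufficient.
- **Data about the procedure:** "hypoxemia is defined as SpO_2_ of 75–89% for < 60 s", while "severe hypoxemia is defined as SpO_2_ < 75% at any time or SpO_2_ of < 90% for > 60 s". No single episode can meet both definitions. No rule is given for classing a patient who has several episodes.
- **Sample size estimation and statistical analysis:** "a proportion of 22% of the patients in the group B is expected to develop hypoxemia", with a fall to 11% assumed for the WNJT. On that basis, "With an α = 0.05 and a power of 80%, we estimated that 140 patients per group would be required". No rate is given for severe hypoxemia. Binary outcomes are compared by a chi-squared test at P < 0.05, with no rule for more than one primary test.
- **Interventions:** the rescue sequence starts "if hypoxemia (SpO_2_ < 90%) occurs". Here the same word covers every desaturation below 90%, mild or severe.

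**The concern.** At least three primary analyses fit this text: the mild category alone, the mild and severe categories as two tests, or a composite of any SpO2 below 90%. They can give different answers on the same data.

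Taken literally, the event that was sized is the defined category, and it leaves out the worst desaturations. A device that turns severe episodes into brief mild ones would add patients to that category while it helps them. If the two categories are tested separately at 5% each and one success is enough, the trial also has two chances of a false positive. In every case, a reader cannot tell which event the 22% and 11% describe.

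**Working it through.** **1. Inputs.** From the sample size section: 22% against 11%, alpha 0.05 (sidedness not stated), power 80%, 140 per group. The split of events into mild and severe is not in the document, so every split below is an assumption.

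**2. The plan's own figure.** For two proportions with pooled variance under the null,

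n = [z_α √(2p̄(1−p̄)) + z_β √(p1(1−p1) + p2(1−p2))]² / (p1−p2)²

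With p1 = 0.22, p2 = 0.11 and p̄ = 0.165, the two roots are 0.5249 and 0.5191.

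- One-sided: (1.645 × 0.5249 + 0.842 × 0.5191)² / 0.0121 = 139.7, so 140. This matches the stated number.
- Two-sided: (1.960 × 0.5249 + 0.842 × 0.5191)² / 0.0121 = 177.6, so 178.

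The unstated one-sided basis is a separate matter. Here it only means that power for the planned effect at 140 per group is 80% one-sided and 70% two-sided.

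**3. Power under two readings of the endpoint.** Assumed split: group B 14% mild + 8% severe, WNJT 10% mild + 1% severe, each patient in one class. Any event is 14 + 8 = 22% against 10 + 1 = 11%, exactly the planned effect.

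Power = Φ{[(p1−p2)√n − z_α √(2p̄(1−p̄))] / √(p1(1−p1) + p2(1−p2))}, n = 140, √n = 11.832, two-sided.

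- Any event, 22% against 11%: (0.11 × 11.832 − 1.960 × 0.5249) / 0.5191 = 0.525, power **70%**.
- Mild only, 14% against 10%: (0.04 × 11.832 − 1.960 × 0.4596) / 0.4587 = −0.932, power **18%**.

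Replacing 1.960 by 1.645 gives 80% and 27%, so the gap does not come from the choice of sides. It depends on the split: with 18% + 4% against 10% + 1%, any event is again 22% against 11%, and two-sided power for the mild category is 49%.

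**4. Direction.** If each patient is classed once by worst episode, the mild rate under the WNJT equals the control mild rate, minus patients spared a mild event, plus patients moved from severe to mild. It rises only when the last term exceeds the middle one. Example (assumed): 12% mild + 10% severe against 17% mild + 2% severe. Severe falls from 10% to 2% and any event from 22% to 19%, but the mild category rises from 12% to 17%.

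**5. Type I error with two tests, either sufficient.** Independent tests: 1 − 0.95² = 9.75%; the upper bound is 5% + 5% = 10%. Simulation of mutually exclusive mild and severe events (140 per arm, two-sided uncorrected chi-squared, 400,000 runs, assumed rates of 12–22% mild and 4–10% severe) gives 9.4–9.5%. If the two tests are any event and severe, it is 8.5–9.1%. A single composite test, or a rule that both must be significant, does not exceed 5% in this way.

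**6. Keeping two primaries.** With alpha of 0.025 each, 22% against 11% needs 216 per group two-sided (178 one-sided), and 140 per group gives 60% (70% one-sided). No sample size can be worked out for severe hypoxemia because no rate is given.

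**The case against.** The strongest reply is that the outcome is named in the singular and one proportion is sized, so a composite is a natural reading. Under it there is neither dilution nor inflation. Testing order may also sit in an analysis plan that is not shown. That is fair, and it makes both consequences conditional. It does not remove the defect: the article's own definition of hypoxemia excludes severe episodes, and the sample size uses that word without qualification.

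Stronger readings that a reader might infer, and why the documents do not support them:

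- **That an effective device will raise the hypoxemia count.** This needs the mild category to be tested alone and more patients moved from severe to mild than spared a mild event. With 14% + 8% against 10% + 1% the mild rate falls, so the usual harm is dilution. The classes also exclude each other by episode, not by patient.
- **That the type I error is 9.75%.** Nothing says that either event suffices.
- **That the rescue trigger is a rival outcome definition.** When SpO2 first drops below 90% its duration is unknown, so a simple threshold for action beside graded outcome classes is coherent. Only the shared word causes confusion.
- **That the 22% belongs to a different endpoint.** The definitions, the primary outcome and the 22% share a cited source that is not available here. One can say only that the article does not state whether severe cases are included.
- **That the trial is underpowered because of this.** Only the gap between readings belongs to this point. Low power from assumed effects smaller than a halving, or from two-sided testing, is a different issue.

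**Conclusion.** The point holds in a limited form: the primary endpoint is badly fixed in the published text. The article does not settle whether the primary comparison concerns the mild category, two events or any desaturation, nor which of these the 22% and 11% describe.

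The choice matters. Under one assumed split that keeps the planned 22% against 11% for any event, two-sided power at 140 per group is 70% on one reading and 18% on another. Reversal is possible but needs a less ordinary pattern. An error rate of about 9.4% to 9.75% follows only if two separate tests are run and either counts as success. The size of the dilution depends on a mild-to-severe split that the article does not give. The unassigned episode of exactly 60 s is a minor gap in the same definitions.

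**What to change.** 1. Define one primary endpoint at patient level: the proportion of patients with at least one SpO2 below 90% during the procedure, mild or severe, each patient counted once and classed by worst category.
2. State whether the 22% and 11% refer to this endpoint. If they do, this change leaves the sample size as it is; if not, restate the assumption and recompute.
3. Make severe hypoxemia a named secondary endpoint, tested only if the primary is significant. Keeping two primaries with a stated multiplicity rule is also defensible, at the cost shown in step 6 of the working.
4. Assign episodes of exactly 60 s to one outcome class.
5. Use a separate term for the rescue trigger so that it is not read as the outcome category. The clinical rule itself stays as written.

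The cost is a wording change in the protocol and registry. Both categories are already due to be recorded, so no new data are needed. At the status date 20 of 308 patients had been recruited. The change should be made before the interim analysis planned at half enrolment.

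### The primary outcome joins two separately defined events but only one is in the sample size, and the article does not say which result decides the trial

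*Protocol article*

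**What the plan says.** Under Primary outcome, and in the same sense in the Abstract: "The primary outcome is the incidence of hypoxemia and severe hypoxemia".

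Under Data about the procedure the two terms are separate classes, each listed as a recorded item. The first: "hypoxemia is defined as SpO_2_ of 75–89% for < 60 s". The second: "severe hypoxemia is defined as SpO_2_ < 75% at any time or SpO_2_ of < 90% for > 60 s". No single episode can belong to both.

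Under Interventions the rescue rule uses the first term more broadly: "if hypoxemia (SpO_2_ < 90%) occurs", with no lower limit and no duration. That covers both classes.

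Under Sample size estimation and statistical analysis, the calculation rests on one event: "a proportion of 22% of the patients in the group B is expected to develop hypoxemia", to be halved to 11% by the device. It continues: "With an α = 0.05 and a power of 80%, we estimated that 140 patients per group would be required for our study". No expected rate of severe hypoxemia is given. Qualitative data are compared by chi-squared test, and a P "value < 0.05 is considered statistically significant". The Discussion states the trial's hypothesis for hypoxemia and related adverse events.

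**The concern.** The primary outcome, the event used for the sample size and the decision rule do not describe the same comparison. At least five readings fit the text:

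- success if either incidence differs;
- success only if both differ;
- one chi-squared test on three classes (none, hypoxemia, severe);
- hypoxemia as defined under Data about the procedure, alone;
- one combined event, any SpO2 below 90%.

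The first does not hold the 5% level. The second and third lose power. The fourth holds 5% but measures the wrong thing if the device shortens episodes: a patient moved from a severe episode to a brief, milder one becomes a new case of hypoxemia, so a benefit counts as harm. Only the fifth gives one test at 5% on an event that falls whenever desaturation is prevented. The trial's main claim depends on which reading is used.

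**Working it through.** **Inputs from the article.** Hypoxemia 22% in group B and 11% in group A; α = 0.05, sidedness not stated; power 80%; 140 per group, 154 after the dropout allowance; chi-squared tests.

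**Assumed, because the article gives no figure.** The severe rate, and that the device halves both incidences. Each patient is placed in one class, the worst reached.

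**Step 1: the plan's own figure.** With p̄ = (0.22 + 0.11)/2 = 0.165,

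n = [z_α √(2p̄(1−p̄)) + z_β √(p1(1−p1) + p2(1−p2))]² / (p1−p2)²

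- √(2 × 0.165 × 0.835) = 0.5249; √(0.1716 + 0.0979) = 0.5191; z_β = 0.8416.
- One-sided: (1.6449 × 0.5249 + 0.8416 × 0.5191)² / 0.0121 = 139.7, so 140. This matches the plan.
- Two-sided: (1.9600 × 0.5249 + 0.8416 × 0.5191)² / 0.0121 = 177.6, so 178.

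The stated 140 is therefore a one-sided calculation for a single event. Two-sided power by the same formula is 70.0% at 140 and 74.1% at 154.

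**Step 2: type I error if either incidence may win.** Two independent tests give 1 − 0.95² = 9.75%. Mutually exclusive classes are slightly negatively correlated, ρ = −√(pq/((1−p)(1−q))). For p = 0.22 and q = 0.05, ρ = −0.122 and the normal approximation gives 9.7%. When severe events are rare, the chi-squared test for them seldom rejects, so the inflation shrinks. Multinomial simulation (200,000 runs per setting, two-sided tests) shows this.

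**Step 3: power if both must win.** Same simulation, both incidences halved.

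Reading A: the 22% is any SpO2 below 90%, and a share of those patients is severe.

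| Severe share of events | Either wins, no effect (140 / 154) | Both win, halved (140 / 154) |
|---|---|---|
| 2% | 5.5% / 5.6% | 0.2% / 0.3% |
| 5% | 7.8% / 8.3% | 2% / 3% |
| 10% | 9.2% / 9.3% | 6% / 7% |
| 20% | 9.5% / 9.7% | 9% / 11% |
| 50% | 9.6% / 9.9% | 13% / 16% |

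Reading B: the 22% is the milder class only, and severe hypoxemia comes on top.

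| Severe rate, group B | Either wins, no effect (140 / 154) | Both win, halved (140 / 154) |
|---|---|---|
| 2% | 9.4% / 9.3% | 6% / 7% |
| 6% | 9.4% / 9.5% | 15% / 17% |
| 10% | 9.6% / 9.8% | 23% / 27% |

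With one-sided tests, both-win power under reading B is higher but still low: 15–38% at 140 and up to 42% at 154.

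**Step 4: the other readings, two-sided, under reading A.**

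- Combined event: type I error 5%; power 71% at 140 and 75% at 154.
- Three-class test, 2 degrees of freedom, severe share 20–50%: power 60% at 140 and 64% at 154.
- Milder class alone: type I error 5%; for severe shares of 20% to 50%, power falls from 59% to 38% at 140 and from 63% to 42% at 154.

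Under reading B the combined event has 75–89% power at 140 and 80–92% at 154 for severe rates of 2–10%. Which event the 22% describes therefore matters for power as well.

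**The case against.** The strongest reply is that the article never announces two primary tests. The outcome is worded in the singular, the rescue rule uses hypoxemia for anything below 90%, and both the sample size and the hypothesis name hypoxemia only. P < 0.05 is a general rule for all comparisons. A combined event, or hypoxemia as the deciding event, fits the text and keeps 5%. This stands. A reader might infer that the trial carries nearly 10% type I error or else far less power than stated; the documents do not support that, because it omits two readings without inflation and rests on a severe rate that they do not give.

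A second reply is that testing order and division of α are commonly left to an analysis plan, which is not shown here. That also stands: their absence is not the point, and it cannot be concluded that the choice would be made after seeing the data. But what the primary event is, and which event was used to size the trial, are stated in the article itself, and those statements do not agree.

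A third reply is that part of the power loss has another cause. This is correct. The combined event's shortfall from 80% under reading A comes from a sample size that matches only a one-sided α, not from having two outcomes.

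**Conclusion.** The point holds as an ambiguity in the primary outcome that needs repair, not as a demonstrated inflation. Two defined, non-overlapping events are primary, one is in the sample size, and the deciding result is not fixed. Under the either-wins rule, type I error is about 5–10%, reaching about 9–10% once at least a tenth of events are severe. Under the both-must-win rule, two-sided power is below about 30% for severe rates up to about 10%, or severe shares up to 50%, if both incidences are halved. One combined event holds 5%. The direction of these results is firm; their size depends on a severe rate that has to be assumed.

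**What to change.** Before the interim analysis at half enrolment, name one confirmatory test: the proportion of patients with any SpO2 below 90% (hypoxemia or severe hypoxemia combined), at 0.05 with sidedness stated. Test severe hypoxemia second at 0.05, only if the first test is significant; otherwise report it as an estimate with its confidence interval. State which event the 22% refers to, and reconcile the definitions under Interventions and Data about the procedure for this purpose.

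The wording takes a few sentences, and the fixed sequence needs no extra patients for multiplicity. Splitting α would cost more: at two-sided 0.025, the 22% versus 11% comparison has 60% power at 140 and 64% at 154.

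There are two costs. No severe-hypoxemia benefit can be claimed if the combined test fails. And if the test is two-sided and the 22% is the combined event, the stated 80% power must be restated as about 71% at 140 or 75% at 154 per group, or the sample size revisited (178 per group evaluable for 80%). That second cost comes from the one-sided calculation and would exist without this change.

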#### Secondary outcomes

The secondary outcomes are the adverse events during the gastroscopy, nasal bleeding or injury, complications, and satisfaction of the anesthetist, physician, and patient.

### Sample size estimation and statistical analysis

The sample size is calculated with the Pass software (version 11.0, NCSS, LLC, Kaysville, UT, USA). The two independent proportions procedure is used. With an α = 0.05 and a power of 80%, we estimated that 140 patients per group would be required for our study. If the dropout rate is set at about 10%, a total of 308 patients (154 in each group) would be required. The incidence of hypoxemia during gastroscopy in obese patients with intravenous propofol anesthesia has been reported to be 22% [20]. Thus, a proportion of 22% of the patients in the group B is expected to develop hypoxemia. P1 and P2 are calculated from the assumption that the WNJT would achieve a reduction from 22% to 11% for the incidence of hypoxemia.

Statistical analysis of data will be performed using the SPSS (Version 23.0, SPSS Inc., Chicago, IL, USA) by a blinded statistician. Continuous variables will be presented as mean ± standard deviation (normally distributed data) or medians and ranges (non-normally distributed data). Numerical data will be compared using a Student’s t-test (normally distributed data) or Mann–Whitney rank sum test (non-normally distributed data). Qualitative data will be expressed as n (%) and compared using a Chi-squared test. A *P* value < 0.05 is considered statistically significant.

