### Randomization and blinding

According to a random number table generated by a computer, patients are randomly assigned to receive either the WNJT (group A) or the nasal prongs (group B). An online random list generation will be utilized to perform blocked randomization in a 1:1 ratio. Outcome assessment and statistical analysis will be performed by independent researchers who are from the Clinical Research Institute of Beijing Friendship Hospital and are blind to the group assignment.

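### The 140 per group gives 80% power only for a one-sided 5% test; the planned chi-squared test has about 70% power

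*Protocol article*

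**What the plan says.** Everything needed is in the protocol article, almost all of it under Sample size estimation and statistical analysis.

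- Target: "With an α = 0.05 and a power of 80%, we estimated that 140 patients per group would be required for our study".
- Method: "The two independent proportions procedure is used", run in PASS 11.
- Effect: "a proportion of 22% of the patients in the group B is expected to develop hypoxemia", and the assumption is that "the WNJT would achieve a reduction from 22% to 11% for the incidence of hypoxemia".
- Dropout: "If the dropout rate is set at about 10%, a total of 308 patients (154 in each group) would be required".
- Analysis: "Qualitative data will be expressed as n (%) and compared using a Chi-squared test", with P below 0.05 taken as significant.

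The Randomization and blinding section gives "blocked randomization in a 1:1 ratio". The article does not say whether the 5% is one-sided or two-sided, either for the calculation or for the analysis.

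**The concern.** The sample size and the analysis should rest on the same test. For a halving from 22%, 140 per group looks small for a two-sided 5% test at 80% power. If the figure was obtained with a one-sided 5% level, it does not give the claimed power for the chi-squared test that the same section names.

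What is at stake is the false-negative risk for the primary outcome. The Discussion says that a negative result would also carry clinical weight. Readers will judge such a result by the stated 80% power, and if the real figure is lower, a non-significant result is weaker evidence against a benefit than it appears.

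**Working it through.** **Inputs.** p1 = 0.22 (nasal prongs), p2 = 0.11 (WNJT), difference 0.11, 1:1 allocation, α = 0.05, power 80% (z = 0.8416). All come from the article.

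**Formula** (pooled variance under the null, no continuity correction):

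n per group = [z_α·A + z_β·B]² / (p1 − p2)²

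- mean proportion = (0.22 + 0.11)/2 = 0.165
- A = √(2 × 0.165 × 0.835) = 0.5249
- B = √(0.22 × 0.78 + 0.11 × 0.89) = 0.5191
- (p1 − p2)² = 0.0121

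**Step 1: reproduce the stated 140.** With one-sided α = 0.05, z_α = 1.645:

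n = (1.645 × 0.5249 + 0.8416 × 0.5191)² / 0.0121 = (0.8634 + 0.4369)² / 0.0121 = **139.7**, rounded up to 140. This is an exact match.

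**Step 2: the same formula, two-sided.** With z_α = 1.960:

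n = (1.0288 + 0.4369)² / 0.0121 = **177.6**, rounded up to 178.

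**Step 3: could another formula explain 140?** Required n per group, rounded up:

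| Formula | One-sided 5% | Two-sided 5% |
|---|---|---|
| Pooled | 140 | 178 |
| Unpooled | 138 | 175 |
| Arcsine | 138 | 175 |
| Pooled, continuity-corrected | 158 | 196 |

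No two-sided version comes near 140.

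**Step 4: power of the planned test.** Power = Φ{[(p1 − p2)√n − z_α·A] / B}. At n = 140, 0.11 × √140 = 1.3015.

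- One-sided: (1.3015 − 0.8634)/0.5191 = 0.844, power 80.1%
- Two-sided: (1.3015 − 1.0288)/0.5191 = 0.525, power **70.0%**

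The two-sided test at other sample sizes, with exact binomial enumeration of the uncorrected chi-squared test as a check:

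| Evaluable per group | Normal approximation | Exact |
|---|---|---|
| 138 | 69.4% | 70.1% |
| 139 | 69.7% | 70.5% |
| 140 | 70.0% | 70.9% |
| 154 (no dropout) | 74.1% | 75.0% |
| 178 | 80.1% | 80.7% |

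**Step 5: the effect that 140 can detect.** Solving the two-sided power formula at n = 140 for 80% gives p2 = 9.8% (normal approximation). Exact enumeration gives 80.3% at p2 = 9.9%. So 80% power applies to a fall from 22% to about 10%.

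**Step 6: the dropout step.** 140 × 1.10 = 154, which is how the article reaches 308. Losing 10% of 154 leaves 154 × 0.90 = 138.6. To retain 140 after 10% loss needs 140/0.90 = 155.6, or 156 per group; 154 covers a loss of 1 − 140/154 = 9.1%. The effect on power is under one percentage point.

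**The case against.** The strongest defence is that the article never says two-sided, and its hypothesis is directional: the Discussion sets out to show that the WNJT lowers hypoxemia, and the sample size section assumes a reduction. On that view a one-sided 5% calculation was intended, and 140 is right. The PASS settings are not shown, so the one-sided origin of 140 is inferred from an exact numerical match.

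This does not rescue the figure. An expected direction is not a one-sided test. The decision rule in the article is an ordinary chi-squared test at P < 0.05, which rejects in both directions. If a one-sided test was meant, the named analysis does not carry it out, so calculation and analysis disagree on either reading. An unseen full protocol or analysis plan cannot make 140 per group give 80% power under the stated test.

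Some of the defence does stand:

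- The dropout shortfall is minor. The article says about 10%, and 9.1% is close to that.
- A continuity-corrected test would have 64.8% power at 140, but the article does not name one, so that figure should not be used to enlarge the shortfall.
- The type I error and the effect estimate with its confidence interval are unaffected. The harm is a higher false-negative risk and a misstated design property.

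**Conclusion.** The concern holds. The stated sample size matches only a one-sided 5% calculation, while the planned test is two-sided. The actual power for 22% versus 11% is about 70% (70.0% approximate, 70.9% exact at 140 per group), not 80%, and it stays below 80% even with no dropout. The evaluable sample is 38 per group short of what the claim needs (178 − 140), about 21% of 178.

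This rests on the article's own rates and allocation, and on reading a chi-squared test at P < 0.05, with no one-sided declaration, as two-sided. It does not depend on the choice between the usual sample size formulas or on the dropout point. It should be corrected because the power claim for the primary outcome is wrong as written.

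**What to change.** State the sidedness and restate the power. Suggested wording:

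> The primary comparison uses a two-sided chi-squared test at the 5% level. With 140 evaluable patients per group, power is about 70% for a reduction from 22% to 11%; 80% power applies to a reduction from 22% to about 10%.

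In the same place, a clause can note that 154 randomised per group allows for 9.1% dropout.

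The test should not be relabelled one-sided after the event to preserve the 80%.

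The correction costs only wording and needs no extra patients; the stated power simply becomes less favourable. Whether to enlarge the trial is a separate decision for the sponsor. Keeping 80% power for 22% versus 11% would take 178 evaluable per group. With 10% dropout that is 178/0.90 = 197.8, or 198 randomised per group and 396 in total, against 308 now. According to Trial status, 20 participants had been recruited by 10 May 2018, so that choice was still open when the article was written.

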### Data collection

#### Patients’ information

Demographic data of patients—including age, gender, body mass index, history of hypertension, diabetes, and coronary artery disease—are collected from the medical records. Airway conditions, ASA physical status classifications, BP, HR, and SpO_2_ before anesthesia are assessed and recorded by a research assistant.

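### The planned unadjusted chi-squared test is valid but leaves recorded baseline data unused; a prespecified adjusted risk difference with a 95% CI would be a cheap improvement

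*Protocol article*

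**What the plan says.** The primary outcome is an incidence (Protocol article, Primary outcome), so the rule for categorical data governs it: "Qualitative data will be expressed as n (%) and compared using a Chi-squared test" (Sample size estimation and statistical analysis). The significance threshold is P < 0.05. That section names no covariate, and no confidence interval for the difference between arms.

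The sample size uses the same unadjusted comparison: "The two independent proportions procedure is used". The assumed effect is that "the WNJT would achieve a reduction from 22% to 11% for the incidence of hypoxemia", and the result is "With an α = 0.05 and a power of 80%, we estimated that 140 patients per group would be required for our study".

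Allocation is described as follows: "An online random list generation will be utilized to perform blocked randomization in a 1:1 ratio" (Randomization and blinding). No stratification factor is named.

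Age and BMI come from the medical records, and "Airway conditions, ASA physical status classifications, BP, HR, and SpO_2_ before anesthesia are assessed and recorded by a research assistant" (Patients’ information).

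**The concern.** The Background and Discussion attribute hypoxemia in obese patients to airway anatomy, reduced lung volume and a less compliant chest wall. Body size and baseline oxygenation are therefore plausible predictors of the outcome, and the trial records both. An analysis that ignores them is less precise than it could be if they do predict hypoxemia.

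This matters more because power under the planned test is already below the stated 80%. The trial is also meant to help anesthesiologists choose an oxygen method. For that they need the size of the reduction and its uncertainty, and two percentages with a P value do not give the uncertainty.

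**Working it through.** **Inputs.** From Sample size estimation and statistical analysis: 22% in group B, 11% in group A, α = 0.05, power 80%, 140 per group. The 22% and 11% are applied to a single binary hypoxemia outcome. The prognostic strength of the covariates is not in the document, so it is assumed over a range.

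**1. The plan's own figure.** With mean risk 0.165:
- √(2 × 0.165 × 0.835) = 0.5249
- √(0.22 × 0.78 + 0.11 × 0.89) = √0.2695 = 0.5191
- n = [(z_α × 0.5249 + 0.8416 × 0.5191) / 0.11]²

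One-sided (z_α = 1.645), n = 139.8, so 140, an exact match. Two-sided (z_α = 1.960), n = 177.6, so 178. Two-sided unpooled and arcsine formulas give 175, and the continuity-corrected one gives 196. No two-sided version tried gives 140.

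**2. Power of the planned test.** A chi-squared test on a 2×2 table is non-directional, so P < 0.05 is two-sided in effect. At 140 per group, (0.11 × √140 − 1.960 × 0.5249) / 0.5191 = 0.525, so power is 70.0%. At 154 per group it is 74.1%.

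**3. Gain from adjustment, by formula.** If covariates explain a share R² of outcome variance, the effective size is about n / (1 − R²). At 140 per group, two-sided:

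| Assumed R² | Power |
|---|---|
| 0 | 70.0% |
| 0.01 | 70.5% |
| 0.05 | 72.2% |
| 0.10 | 74.6% |
| 0.20 | 79.4% |

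Reaching 80% by adjustment alone needs R² = 1 − 140/178 = 0.21.

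**4. Gain by simulation.** 3,000 trials per row, 140 per group, four normal covariates, marginal risks held at 22% and 11%:

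| c-statistic (R²) | Chi-squared | Adjusted likelihood-ratio test | Standardised risk difference |
|---|---|---|---|
| 0.50 (0) | 71.3% | 72.0% | 71.9% |
| 0.64 (0.041) | 70.4% | 72.7% | 72.6% |
| 0.74 (0.139) | 71.1% | 76.3% | 76.7% |
| 0.82 (0.251) | 69.8% | 80.7% | 80.9% |

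Monte Carlo error is about √(0.7 × 0.3 / 3000) = 0.8 points. A second simulation (6,000 trials, one prognostic score, Wald test) gave 70.4% adjusted against 71.2% unadjusted with no prognostic value, a loss of 0.8 points. A third, with three covariates as in the fix, gave 70–72% unadjusted. Adjusted power was essentially unchanged for null or weak covariates and about 3 to 9 points higher for moderate to strong ones.

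**5. Type I error.** With 22% in both arms, rejection was 4.8–5.6% for chi-squared, 5.0–5.8% for the adjusted likelihood-ratio test and 4.9–5.8% for the standardised risk difference.

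**6. Room in the model.** Expected events are 0.22 × 140 + 0.11 × 140 = 30.8 + 15.4, about 46. Arm plus three covariates makes four terms, about 11.5 events per term.

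**7. What an interval would show.** At observed rates of 22% and 11%, SE = √(0.2695 / 140) = 0.0439. The difference is 11 points ± 8.6, or about 2 to 20 points.

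**The case against.** The strongest reply is that the article states nothing wrongly. The chi-squared test matches both the randomisation and the sizing procedure, and adjusted models and intervals are often left to an analysis plan, which is not shown here. The first part stands: this is an improvement to a named method, not a contradiction. The second part stands in that the missing interval is not an error. But the article does fix the test for the primary outcome, and a better one is available from data already being collected.

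A reader might infer that chance imbalance in BMI or baseline SpO2 biases the planned comparison. It does not. The test's error rate already allows for chance imbalance, and the null simulations agree.

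A reader might also infer that adjustment is sure to recover lost power. The document gives no prognostic strength for any covariate, and there are reasons to expect little. Entry is limited to ages 18–65, ASA I–II and BMI of at least 30, and every patient is preoxygenated to a common target, which may weaken the link between baseline SpO2 and later desaturation. The Background says obese patients desaturate more than others, not that risk rises with BMI among the obese. BMI has no stated upper limit, so it can still vary widely, but the gain could be near zero.

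Nor is the change entirely free. The event count limits the covariates, missing values need a rule, and a logistic coefficient alone is a conditional odds ratio, not the 22% versus 11% contrast. Standardisation deals with that last point.

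**Conclusion.** The point holds as a low-cost improvement. At 140 per group, two-sided power would go from about 70% to about 70–76% for weak to moderate covariates (c-statistic up to about 0.74). The loss would be under 1 point if they are not prognostic. These figures rest on assumed prognostic strength and on 22% versus 11%. The case for an interval does not depend on the covariates.

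The tempting stronger reading, that adjustment makes up the power shortfall, is not supported. The shortfall arises because 140 per group reproduces only with a one-sided alpha of 0.05, while the planned test is two-sided in effect. Closing it at 140 per group by adjustment alone would need R² of about 0.21, and nothing in the document suggests that.

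**What to change.** Before the interim analysis at half enrolment (154 of 308 patients), prespecify:

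- **Primary analysis:** a logistic model with arm, BMI, age and baseline SpO2, the last three continuous.
- **Deciding result:** the standardised (marginal) risk difference with its 95% CI, named as the basis of the primary conclusion.
- **Sensitivity analysis:** the chi-squared test as now planned.
- **Missing covariate values:** one simple rule, fixed in advance.

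Keep the covariates to these three, given about 46 expected events. Airway conditions are also recorded, but the article does not say how they are coded. Substituting or adding them would need a fixed coding and attention to the event count.

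The cost is analysis-plan wording and one standardisation step after the logistic fit. No extra patients or data are needed. The article reports 20 recruits by 10 May 2018, so at that date there was ample time before the interim analysis.

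Separately, state the sidedness of the sample size calculation, and either re-size (178 per group before dropout for 80% two-sided power) or justify about 70%.
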